# B1. PURPOSE OF PROTOCOL

| To evaluate the effects of Tai Chi—a mind-body exercise––on age-related loss of physiological complexity (using fractal and entropy based measures), and to understand the relationship between complexity, function and adaptability, we will conduct a two-arm prospective randomized clinical trial. Our overarching goal is to evaluate if six months of Tai Chi training, compared to a waitlist control receiving standard medical care, can enhance physiological complexity and adaptability in older Tai Chi-naïve adults. Secondary goals of the study are to characterize the relationship between complexity biomarkers, measures of function, and resilience. This pilot study will inform a future more definitive trial by providing information on recruitment and retention, compliance, dose-dependent effects, preliminary estimates of effect size, and the optimal biomarkers of complexity, function, and adaptive capacity.    **Specific Aim #1: To determine if 6 months of Tai Chi training can increase complexity, function, and adaptive capacity of multiple physiological systems in older healthy adults.** Sixty healthy older adults (50-79y) naïve to Tai Chi will be recruited from the Boston community and randomized to either 6 months of Tai Chi training or to a waitlist control. Measurements of complexity, adaptive capacity, and function will be assessed at baseline, 3, and 6 months. Dynamics of cardiovascular (heart rate), balance (center-of-pressure displacement), and locomotor (gait stride interval) systems will be quantified using indices derived from two complementary analytic methods developed by members of our team––detrended fluctuation analysis^26^ and multi-scale entropy.^6^ Function will be characterized by exercise capacity, clinical measures of balance, lower and upper extremity strength, cognitive function, and health related quality of life. Adaptability of multiple physiological systems will be assessed using common perturbations including: heart rate responses to posture change, center of pressure (i.e. balance) responses to a dual cognitive task and closed eyes, and c) gait responses to dual cognitive task. In addition to informing the feasibility of a future trial, outcomes will provide preliminary data to evaluate the following hypotheses.  ***Hypotheses*** *Compared to the control group:*  *H.1.a) Those who participate in Tai Chi will exhibit higher levels of complexity across all measured physiological systems;*  *H.1.b) Those who participate in Tai Chi will exhibit higher levels of physical and cognitive function;*  *H.1.c) Those who participate in Tai Chi will exhibit higher levels of adaptive capacity;*  *H.1.d) The magnitude of the effects of Tai Chi on physiological complexity, function and adaptive capacity in healthy older adults will be positively correlated with age.*  **Specific Aim #2: To determine the relationships between biomarkers of physiological complexity, conventional measures of function and adaptive capacity.** Statistical regression models will be used to determine relationships, both at baseline and overtime, between a) complexity biomarkers and measures of physical and cognitive function, and b) complexity biomarkers and adaptive capacity. Elucidating these relationships will further inform the interpretation of complexity biomarkers and provide insights into underlying component mechanisms contributing to complex physiological dynamics.  ***Hypotheses*** *At baseline:*  *H.2.a) Measures of complexity are positively correlated with physical and cognitive function;*  *H.2.b) Measures of complexity are positively correlated with adaptive capacity.*  *Over time:*  *H.2.c) Changes in complexity are positively correlated with changes in physical and cognitive function;*  *H.2.d) Changes in complexity are positively correlated with changes in adaptive capacity.*  **Specific Aim #3: To determine cross-sectionally if long-term Tai Chi training (> 5 years) is associated with greater complexity, function, and adaptive capacity of multiple physiological systems in older healthy adults, when compared with Tai Chi naïve and novice (≤ 6 months training) Tai Chi practitioners**  ***Hypotheses*** *Compared to Tai Chi naïve and novice Tai Chi practitioners:*  *H.3.a) Long-term Tai Chi practitioners will exhibit higher levels of complexity across all measured physiological systems;*  *H.3.b) Long-term Tai Chi practitioners will exhibit higher levels of physical and cognitive function;*  *H.3.c) Long-term Tai Chi practitioners will exhibit higher levels of adaptive capacity;*  *H.3.d) The magnitude of the effects of long-term Tai Chi training on physiological complexity, function and adaptive capacity in healthy older adults will be positively correlated with age.*  **Specific Aim #4: To determine cross-sectionally if age is associated with greater complexity, function, and adaptive capacity of balance and gait in young healthy adults, when compared with to older adults**  ***Hypotheses*** *Compared to older adults and a young adult comparison group:*  *H.3.a); The magnitude of physiological complexity, function and adaptive capacity will be positively correlated with age.*  *H.3.b) Young adults will exhibit higher levels of adaptive capacity of balance and gait.* |

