#### B3. DESCRIPTION OF RESEARCH PROTOCOL

##### Study Design – Overview, Methods, Procedures

| We propose a two-arm prospective randomized clinical trial with non-randomized third group to evaluate the effect of Tai Chi on age-related loss of complexity.    **Arms 1 and 2**  will consist of a total of 60 Tai Chi–naïve healthy older adults (aged 50-79) will be randomized to either six months of Tai Chi training, or to a waitlist control receiving standard medical care. Our primary outcomes are complexity-based measures of cardiovascular (heart rate, HR), balance (center of pressure, COP) and locomotor (stride interval) dynamics assessed at 3 and 6 months. Secondary outcomes include measures of physical and psychological function and tests of physiological adaptability also assessed at 3 and 6 months. A secondary goal of this study is to characterize the relationship between complexity biomarkers, measures of function, and adaptability. This pilot study will inform a future more definitive trial by providing information on recruitment and retention, compliance, dose-dependent effects, preliminary estimates of effect size, and the optimal biomarkers of complexity, function, and adaptive capacity. Figure 1 summarizes the overall study design.  **Arm 3** (Tai Chi Expert Group): A total of 30 healthy older adults (aged 50-79) each with over 5 years of Tai Chi practice will comprise the third group of this study. In a single visit, primary outcomes related to complexity-based measures of cardiovascular (heart rate, HR), balance (center of pressure, COP) and locomotor (stride interval) dynamics), as well as secondary outcomes related to physical and psychological function and tests of physiological adaptability will be assessed. This group of Tai Chi experts will serve as a ‘gold standard’ of what the long-term physiological impacts of tai chi training might provide, and thus serve as an informative reference population to our current Tai Chi Naïve and Tai Chi Novice (i.e. after 6 months training) groups.  **Arm 4** (Young Comparison Group): A total of 15 healthy young adults (aged 25-35) with no prior Tai Chi experience will comprise the fourth group of this study. In a single visit, primary outcomes related to complexity-based measures of balance (center of pressure, COP) and locomotor (stride interval) dynamics, as well as secondary outcomes related to physical function and physiological adaptability will be assessed. This group of healthy young adults will serve as a reference comparison group for balance and gait measures before any age-related decline begins.  **Tai Chi intervention**  All Tai Chi instruction will take place at one of the Tai Chi schools within our research network, which was established and used in a prior NIH funded Tai Chi trial of ostepenic women (BIDMC protocol # 2007P––000162). These schools were chosen to meet specific criteria ensuring they provide valid, stable Tai Chi programs led by experienced teachers. Importantly, since participants are being asked to make a six month commitment to Tai Chi training, allowing them to receive training at a school they choose within their community will increase the likelihood of protocol adherence. Administering the intervention through community Tai Chi schools also affords a high level of ecological validity, as participants will be exposed to a number of traditional components of Tai Chi training that are often absent in fixed protocols provided in medical settings.^77,152^ Finally, because of the inclusion of multiple Tai Chi instructors and well-defined but slightly varying protocols, the results of this study will have good generalizability—applying not only to a single protocol of Tai Chi taught by one teacher, but to a range of approaches that share a common, well-defined set of criteria.  Participants randomized to Tai Chi will be required to attend, on average, two classes per week over the six months of the intervention. They will also be asked to practice a minimum of 30 minutes, two additional days per week. The majority of schools in our network provide DVD’s or printed materials to facilitate home practice. Compliance with this training schedule will be monitored using a combination of class attendance cards that are signed by Tai Chi instructors following each visit, and participant-completed home practice logs employing protocols developed in our current Tai Chi for osteopenia study. Participants will be asked to send class attendance and home practice logs to study staff monthly using prepaid envelopes provided at the beginning of the study. If attendance and/or practice logs are not submitted on time, the study coordinator will call the participant within 7 days of the due date. Effort will be made to keep subjects actively engaged in the protocol. If a participant is non-compliant, the study coordinator will contact the participant and work with them to overcome any barriers to participation.  **Measurement protocols**  Overview of measurement protocol  All three arms of the study will complete our baseline measurement protocol including acquisition of 1) steady-state dynamics of the cardiovascular, locomotor and balance control systems, 2) measures of the ability of these systems to respond to imposed stressors, and 3) more traditional measures of function and Health Related Quality of Life (HRQOL). Additionally, traditional linear outcome measures for heart rate variability, gait, and balance will be assessed for comparison with complexity measures. All measurements will be assessed at baseline. Only Arms 1 and 2 (Tai Chi Novices and Control Group) will repeat all measures at 3 and 6-months. All outcome assessors will remain blinded with respect to treatment allocation. Table 1 provides a summary of these measures, as well as additional screening tools.  **Table 1. Summary of outcomes and measures and associated variables (see below)**   \| **Temporal dynamics during steady-state conditions** \| **Physiological measure** \| **Testing methods** \| **Outcome variable** \| \| --- \| --- \| --- \| --- \| \|  \| Heart rate (HR)º \| Beat-to-beat variation measured using ECG for a 30 minute during seated quiet resting \| HR complexity \| \|  \| Standing balance \| Center of pressure (COP) dynamics during quiet standing with eyes open \| COP complexity \| \|  \| Gait \| Stride–to-stride interval at preferred speed during a 20 minute period \| Stride complexity \| \| **Adaptive capacity** \| Heart rateº \| Sit to stand test \| Max change in heart rate \| \|  \| Standing balance \| Eyes closed  Cognitive dual task \| Change in COP complexity  Change in magnitude of COP  displacement \| \|  \| Gait \| Cognitive dual task \| Change in average stride  variability \| \| **Function and HRQOL** \| Exercise capacity \| Max walking speed \| m/sec \| \|  \| Musculoskeletal strength/power \| a. Lower extremity power (Jump test)  b. Grip strength (dynamometer) \| a. Maximum height of  jump (cm)  b. kg \| \|  \| Timed Up and Go (TUG) \| Standardized test of time to rise from chair, walk 10 feet to and from cone, return to seated position \| Functional status \| \|  \| Functional reach \| Subject reaches forward with hand and arm  extended and parallel to a yardstick at  shoulder height to reach as far as possible without taking a step \| Functional Status \| \|  \| Clinical balanceº \| Single leg balance with eyes open and closed \| Maximum time on balance \| \|  \| Range of motionº \| a. Goniometry of lower extremity (hips, knees, ankles bilaterally)  b. Sit and reach test (back and leg flexibility) \| a. Degrees of motion  b. cm \| \|  \| Respiration rateº \| Nasal thermoster attached to volume gas monitor \| Breathing frequency \| \|  \| Electrical potential \| Skin surface electrical potential \| Skin surface electrical potential at select segments along arms and legs \| \|  \| Moodº \| Profile of Mood States \| Indices of 6 domains of mood \| \|  \| Cognitive functionº \| Trail Making Test A and B  Controlled Oral Word Association Test  Backwards Digit Span Test \| Time to complete test (sec)  Number of words recalled/min  Number of digit sequences  correctly repeated \| \|  \| HRQOLº \| SF-36 \| Indices of physical and  mental health in 8 domains \| \|  \| Physical activityº \| Physical Activity Status Scale  Arm 3 ONLY: Frequency of Tai Chi and related exercise training \| Index of physical activity  during prior week \| \| **Protocol adherence, screening, and potential confounders** \| Tai Chi training*º \| Teacher reported class attendance records  Self-reported home practice logs \| Numbers of classes/month  Hours of home practice/month \| \|  \| Cognitive function \| Mini-mental state exam \| Index reflecting 5 domains of  cognitive health \| \|  \| Expectancy regarding intervention*º \| Expectancy/credibility questionnaire \| Numerical scale (1-5) \| \|  \| Satisfaction regarding intervention*º \| Satisfaction questionnaire \| Numerical scale (1-5) \| \|  \| Exit Interview*º \| Qualitative exit questions concerning study experience. \| Six open-ended questions \|   (Key provided on following page)  * Arm 3 (The Tai Chi Expert Group) will not be subjected to these measures.  º Arm 4 (Young Comparison Group) will not be subjected to these measures.  Flow of participant through protocol measurements (Arm 1,2, and 3)  All testing will take place in the Syncope and Falls in the Elderly (SAFE) laboratory, located within the CRC at BIDMC. Subjects will be asked to arrive at the laboratory between 8:00 -10:00 a.m. We expect testing to occur for approximately 4 hours. Participants will first meet with a CRC study nurse who will confirm eligibility questions asked during the phone screen. A study investigator will then ask participants to review and sign the informed consent form. The CRC study nurse will then review participant’s health history, obtain vital signs, ECG, height and weight. Study personnel will implement the mini-mental state exam. Participants that meet all eligibility criteria will then undergo standard study related measurements that will be conducted by [name] and/or a TBD research assistant, with oversight by [name], the SAFE laboratory director.  The sequence of testing we will employ is based on protocols regularly conducted in the SAFE laboratory,^140,153^ and has been designed to minimize fatigue and patient burden, and maximize the quality/validity of the data collected. Each stage of testing, as well as repeated assessments of specific tests, will be separated by an appropriate resting period. The total time for completion of measurements is estimated to be 4 hours. The general order of procedures is as follows:  a. Fitting of HR instrumentation, measurement of resting HR dynamics, sit-to-stand test, and timed up and go test  b. Steady state and challenged center of pressure (balance) testing  c. Preferred speed stride dynamics and dual task walking  d. Break with snack  e. Completions of cognitive, mood, HRQOL, and exercise behavior instruments  f. Physical function tests (maximum walking speed, balance, jumping height, grip strength, range of motion)  Flow of participant through protocol measurements (Arm 4 – Young Comparison Group)  All testing will take place in the Syncope and Falls in the Elderly (SAFE) laboratory, located within the CRC at BIDMC. We expect testing to occur for approximately 2 hours. Participants will first meet with a CRC study nurse who will confirm eligibility questions asked during the phone screen. A study investigator will then ask participants to review and sign the informed consent form. The CRC study nurse will then review participant’s health history, obtain vital signs, height and weight. Study personnel will implement the mini-mental state exam. Participants that meet all eligibility criteria will then undergo standard study related measurements that will be conducted by [name] and/or a TBD research assistant, with oversight by [name], the SAFE laboratory director.  The sequence of testing we will employ is based on protocols regularly conducted in the SAFE laboratory,^140,153^ and has been designed to minimize fatigue and patient burden, and maximize the quality/validity of the data collected. Each stage of testing, as well as repeated assessments of specific tests will be separated by an appropriate resting period. The total time for completion of measurements is estimated to be 2 hours. The general order of procedures is as follows:  a. Timed up and go test  b. Steady state and challenged center of pressure (balance) testing  c. Preferred speed stride dynamics and dual task walking  d. Physical function tests (maximum walking speed, balance, jumping height, grip strength, range of motion)  Details of measurement procedures  *Cardiovascular measures:* Steady-state HR dynamics will be assessed during seated rest with spontaneous breathing. To collect the sufficient number of heartbeat cycles for complexity measures, HR will be assessed for 30 minutes. Additionally, two 5-minute periods of HR dynamics will also be assessed during paced breathing (15 and 6 breaths per minute); paced breathing will enable the assessment of cardiovascular dynamics and linear measures of HR variability while controlling for the potentially confounding effects of respiration.^154^ During each breathing pattern, HR and respiration patterns will be simultaneously measured. Heart rate will be recorded using a 3-lead electrocardiogram attached to a light-weight (<300 g) wearable ME6000 data acquisition computer (Mega Elektronika, Inc). Respiration will be measured using a nasal thermistor attached to an infrared end-tidal volume gas monitor (Capnomac Ultima, Ohmeda Inc.). Beat-to-beat blood pressure will be measured from a cuff placed on the finger using a Portapress-2 device (FMS, Inc), and galvanic skin conductance will be measured using an AD Instrument MLT116F (AD Instrument, Colorado Springs, CO).  The effects of perturbation to the cardiovascular system will be evaluated from the well-validated sit-to-stand test.^155^ Standing following prolonged sitting (≥5 min) results in an immediate elevation in HR, with relative greater change in HR response reflective of impaired cardiovascular regulation. The maximum change in HR (ΔHR) evoked from the sit-to-stand test will be quantified. ΔHR will be calculated by subtracting the minimum HR during sitting from the maximum HR during the subsequent bout of 1 min standing.  *Balance measures:* Steady-state standing balance dynamics will be assessed during eyes-open quiet standing as well as sitting. With arms at the side and bare feet shoulder width apart, subjects will be asked to stand as still as possible and to visually fixate on an “X” drawn on a wall approximately 3m away at eye-level. Center of pressure (COP) displacement will be recorded with a standard force plate (Kistler Instruments Corp, Amherst, NY). To collect sufficient COP data for complexity analysis, 1 min of continuous standing will be completed. This protocol will repeat for the sitting component of the test, with modifications made for the now seated subject.  The effects of visual and cognitive perturbations will also be evaluated. For the visual perturbation, subjects will stand similar to above, except with eyes-closed.^58^ For the cognitive perturbation, subjects will perform the dual task of counting backwards, out loud, in multiples of three, while attempting to repeat the steady-state protocol. Subjects will wear an MP3 recording device attached to their person or nearby to record verbal dual task cognitive test performance. This cognitive dual-task is commonly used to challenge standing balance in both healthy and movement disordered populations.^72^ To avoid potential effects of learning, subjects will begin each trial from 500, 499, or 498, in random order.  To account for potential trial-to-trial variability, three 1 min trials will be completed for each condition (steady-state, eyes-closed, dual task). Trials will be randomized and at least one minute rest will be given between each trial. During the first trial, the subject’s feet will be outlined with chalk to ensure consistent foot placement. A trained spotter will provide stabilizing assistance if necessary.  As one's balance is influenced by breathing, the effects of breathing frequency on standing balance will also be examined during one 4 min trial of standing on the force plate. Following 30sec of normal breathing, subjects will be asked to breath in rhythm to a metronome for three minutes. Metronome frequency will change every 30sec to obtain the following breathing frequencies: 50, 40, 30, 20, 10 and 5 breaths/min. A final 30sec of normal breathing will be completed to finish the test. The subject will be given time to practice breathing in rhythm to the metronome prior to the test. They will be reminded to return to their normal breathing patterns should they feel uncomfortable or light-headed during the test, and encouraged to sit or rest at any time. A trained spotter will remain behind the subject at all times.  *Gait measures:* Steady-state gait dynamics will be assessed during over ground walking at preferred speed. Subjects will walk along a long corridor (~75m) that is wide enough (~5m) to enable smooth turning. To record consecutive stride-to-stride durations, subjects will have foot-switches (Mega Elektronika, Inc) inserted into the shoes and the ME6000 data acquisition monitor attached to the waist. To collect the sufficient number of steps required for complexity measures, 20 min of continuous walking will be completed.The effects of a locomotor perturbation on gait speed, an indicator of gait health and overall function,^156^ will be assessed during continuous over ground walking while performing the same cognitive dual task as in balance testing. Subjects will complete three 1 min trials while counting backwards, out loud, in multiples of three.^157^ Dual tasking decreases walking speed.^72^ The distance walked during each trial will be recorded and used to calculate average speed. *Assessment of function and health-related quality of life*  Multiple clinical tests of physical and mental function will further characterize the sample, evaluate correlations between complexity measures and function, and assess the impact of Tai Chi and age on these outcomes.  *Maximum Walking Speed*: Performance in this common, easily administered clinical test is associated with functional decline.^158^ Subjects will walk in a straight line as fast as possible, without running, on a pre-measured 11m course. The time taken to walk 5m, from the 3m to 8m mark will be recorded and used to calculate maximal walking speed (m/s).  *One-legged standing balance*: This test will be assessed according to Vereeck et al.^159^ Timing will start when the subject has assumed the proper position on their preferred leg and verbally indicates readiness to begin the test. Timing will stop when the subject disengages from the starting position (i.e., the suspended foot touches the floor or the hands touch support surface) or when the 30 sec time limit is reached. The test will be conducted in the corner of a room, and the subject will be instructed to reach for the wall should they feel unstable. Three trials will be completed for eyes-open and eyes-closed conditions, and the greatest duration (sec) for each condition will be used for analysis. This test has been correlated with fall risk in older adults.^160^  *Lower-Extremity Muscular Power*: Maximal power output of the lower extremities will be estimated by assessing maximum vertical jump height (m) according to Bosco.^161^ In a study of more than 6000 women and men aged 40 to 85 years, Fujita et al^162^ determined this test to be safe for community-dwelling older adults, and that those with relatively low vertical jump scores had higher mortality rate over the six year follow-up period. Furthermore, as compared to lower-extremity muscular strength, power appears to be closely related to fall-risk^163^ and physical function.^164^ Subjects will complete a standard warm-up consisting of five sub-maximal jumps. Subjects will then complete three countermovement jumps on a stationary Kistler force plate (Kistler Instruments Corp, Amherst, NY). The “flight-time” for each jump, determined from the force plate reading, will be used to determine the maximum height reached by the subject’s center of mass using the Bosco method.^161^  *Range of Motion*: Bilateral hip, knee, and ankle joint passive range of motion (degrees) will be measured by a trained investigator ([name]) using a goniometer and standard procedures^165^ Lower body flexibility will also be assessed using the validated Chair Sit and Reach test.^166^  *Electrical Potential:* Skin surface electrical potential will be measured at select segments along the arms and legs, using 8 surface band electrodes (EL-506, Biopac, Goleta, CA) – 2 electrodes per extremity.  The electrodes will be connected to a data acquisition unit (Powerlab ML-880, AD Instruments, Colorado Springs, CO). This procedure tests the hypotheses exploring relationships between electrical potential and dynamics of other physiological measures (e.g. blood pressure and breathing).  *Physical Activity Levels:* In addition to Tai Chi training, general daily physical activity levels may influence both physical and cognitive function. The amount and intensity will therefore be recorded using the Physical Activity Status Scale (PASS).^167^ The PASS scale is an extension of the four-category scale used by Jones and associates^168^ to quantify leisure exercise levels. Each subject will be asked to estimate his or her general physical activity during the previous week using an 11-point scale (i.e., 0-10). The scale quantifies physical activity duration by a combination of the minutes of exercise per week and the intensity of this exercise (heavy, modest, or none). The concurrent validity of the scale has been documented in both men and women and scores correlate with maximal oxygen consumption in younger and older adults.^169,170^  *Grip strength:* Maximum grip strength is widely considered a simple and reliable measure that is correlated with mortality/survival, and disability, and overall function in middle-aged and older adults.^171^ Grip strength will be measured using a handgrip dynanometer Grip D (Takei Scientific Instruments, Tokyo, Japan). Subjects will be asked to grip the instrument with their dominant hand with maximum force. Measurements will be recorded to the nearest 0.5 kg, repeated three times and averaged. *Timed Up and Go Test:* This is a validated test for quantifying functional mobility that may also be useful in following clinical change over time. Patients begin in a seated position, stand up from a chair, walk a short distance (3 meters, ~10 feet) at a comfortable pace, turn around, return, and sit down again. This test will be timed by the blinded research assistant. The patient will repeat the test and the times will be averaged. The test is quick, requires no special equipment or training, and is easily included as part of the routine medical examination. *Functional Reach:* This standardized test is a measure of balance and is the difference, in inches, between arm's length and maximal forward reach, using a fixed base of support (such as a wall). This test can be used to detect balance impairment, change in balance performance over time, and in the design of modified environments for impaired older persons. The test utilizes a 48-inch measuring device or "yardstick".A reach of less than or equal to a certain level could be predictive of fall risk.  *SF36*: This health-related QOL instrument consists of 36 multiple choice items scored on a 0 to 100 scale of improving health status for each of 8 domains: physical functioning, role limitation due to physical problems, bodily pain, general health, vitality, social functioning, role limitations due to personal or emotional problems, and mental health. The SF-36 has been validated in a variety of populations including young and old healthy individuals, and patients with chronic medical problems, and has good test-retest reliability.^172,173^  *Cognitive function*: Cognitive function will be assessed with validated measures of executive function, working and short-term memory. The Trail Making Test (TMT) is a widely used instrument that is administered in two parts.^174^ TMTa is a visual-scanning task; the time required to draw lines sequentially connecting numbered circles from 1 to 25 is recorded. TMTb assesses time required to connect the same number of circles in an alternating sequence of numbers and letters. TMTb is considered to evaluate executive control, and is correlated with other executive function measures.^175^ TMT is a sensitive indicator of overall neurological impairment,^174^ and has good reliability.^176^ The Controlled Oral Word Association Test (COWAT) examines working memory span.^177^ COWAT requires the participant to produce as many words as possible that begin with a given letter of the alphabet (F,A,S). There is 1 minute allowed for each of the three letters. The score is the sum of all acceptable words produced in the three trials. COWAT has good reliability and validity.^177-179^ The Backwards Digit Span Test (BDS) is a widely used measure of short-term memory, i.e. the number of digits a person can absorb and recall in correct serial order. Two trials of eight number sequences are read aloud. The number sequences start out easy, with just two numbers, and get progressively more difficult, the last being nine digits. Scores are based on the number of sequences correctly recalled (i.e., until the participant consecutively fails two trials of the same digit span length). BDS has good reliability and validity.^177^ All three measures have been employed in studies evaluating the impact of exercise on cognitive function in elders.^1,2^  *Mini-Mental State Examination (MMSE)*: This is a short assessment instrument used to grade cognitive function (orientation to time and place, registration, memory, attention and concentration, praxis, constructional and language capacity, ability to follow commands).^180^ It is used widely in primary care and in community based research settings.^181,182^ The inter-rater reliability of the MMSE is 0.83.^180^ MMSE will be used only as a screening tool; only participants with scores ≥24 will be included.  *Profile of Mood States (POMS):* This is a well-validated instrument for assessing emotional states that are transient and expected to respond to clinical intervention.^185^ It has been widely used to assess the effects of exercise interventions. The instrument consists of 65 single-word items rated on a 5-point scale to indicate recent mood in 6 dimensions: tension/anxiety, depression/dejection, anger/hostility, vigor/activity, fatigue/ inertia, and confusion/bewilderment. A decreased total score denotes an improved emotional state. Test-reliability coefficients are reported to range from 0.65 to 0.74.^185^ Studies of Tai Chi have reported improvement in mood, decrease in anxiety, and enhancement in vigor as measured by the POMS scale.^186^  *Expectancy and Satisfaction*: We will assess the degree to which participants believe that Tai Chi will be beneficial to their health using an instrument used in a number of prior CAM studies. Participants in both groups at baseline will be asked: ‘How confident are you that Tai Chi will improve your health?’; ‘How confident are you in recommending Tai Chi to a friend for health promotion?’; ‘Does doing Tai Chi for health make sense to you?’. Response choices range from 1 through 5, with 1 representing ‘not at all’ confident and 5 ‘extremely’ confident. For participants in the Tai Chi group, satisfaction with the intervention will be assessed by asking them to score the following four statements (5 point scale; 1 strongly agree, 5 strongly disagree) at 3 and 6 month visits: ‘Overall, I am satisfied with my Tai Chi experience in the study’; ‘Overall, I am satisfied with my Tai Chi school’; ‘Overall, I am satisfied with the tai chi teachers I am training with’; ‘I would recommend the Tai Chi program I am enrolled in to a friend or relative.’  *Qualitative Exit Interview:* At the end of your 6 month visit, subjects assigned to the Tai Chi group will also be asked to complete a qualitative exit questionnaire comprised of 6 questions. We will audio tape the answers to these questions. The audio file will be erased once it has been transcribed, within a year of the interview date. Subjects may decline any question they do not wish to answer, and they may decline from having their answers audio taped.  **Survey regarding control groups for future studies**  At the end of our initial phone screen, all participants will be asked a series of questions to explore the types of activities they would consider worthy of participating in, and willing to be randomized to, in a future hypothetical trial related to healthy aging. A list of specific activities (e.g., exercise classes at local YMCA’s, academic lecture series on healthy aging, and group walking classes) will be presented, and for each activity, participants will be asked to respond with one of the following assessments: very interested in participating, moderately interested in participating; not at all interested in participating. Results from this survey will help determine the controls we might employ in a follow-up multi-arm study.  **Data processing**  Analog signals from the ECG and balance platform will be recorded at 1000 Hz using Labview NIDAQ software (National Instruments Data Acquisition System 64 Channel/100 Ks/s, Labview 6i, Austin, TX). Foot switch signals will also be recorded at 1000 Hz using the ME6000 and accompanying software.  For cardiovascular measures, beat-to-beat HR will be determined from the R-wave on the ECG. All data will be visually inspected for accuracy of R-wave detection, artifacts and occasional extra-systoles using software written in our laboratory. Ectopy and artifacts will be removed using a linear interpolation algorithm. The HR interval time-series will be used to compute steady-state complexity measures. For comparison with complexity measures, HR data will also be analyzed using spectral analysis methods we have developed and employed in our prior studies.^137,144^  For balance measures, the acquired anterioposterior (AP) and mediolateral (ML) (COP) time series will be digitally filtered with a zero-lag fourth-order Butterworth low-pass filter with a 5 Hz cutoff frequency. AP and ML COP time-series will be used to compute steady state complexity measures (see D.6). For comparison with complexity measures, the traditional measures of average displacement (mm) in the AP and ML directions will also be determined by computing the mean scalar displacement along each axis.^189^ To assess the effects of visual and cognitive perturbation, average ML and AP displacement will also be calculated for the eyes-closed and dual task conditions. As each perturbation increases the magnitude of COP displacement, the effect of perturbation will be defined by the percent change in average ML and AP COP displacement during the perturbation condition as compared to the steady-state condition.  For gait measures, on/off foot switch data will be used to determine consecutive stride durations (time from initial contact of one foot to the subsequent contact of the same foot) during the 20 min walk. The resulting stride duration time series will be used to compute steady-state complexity measures. To assess the effects of the dual task perturbation (known to decrease walking speed), the percent change in walking speed during dual task as compared to the steady state condition will be computed.  **Computation of complexity measures**  Our team has extensive experience quantitatively analyzing complex physiologic signals – particularly for signals to be obtained in this study. Two principal complexity metrics––Detrended Fluctuation Analysis (DFA) and Multiscale Entropy (MSE)––were developed by team members.^6,26,51^ DFA quantifies long-range correlation properties (fractality) of a signal. Unlike alternative approaches (e.g., Fourier spectral analysis and Hurst analysis), DFA permits the detection of intrinsic self-similarity embedded in a seemingly nonstationary time series. DFA has been successfully applied to a wide range of simulated and physiologic time series in recent years.^5,13,18^ Multiscale Entropy quantifies the information content of a signal over multiple scales. Compared to other entropy-based methods, MSE uniquely accounts for dynamical information encoded in physiologic signals over multiple scales and therefore is able to distinguish between highly irregular random (uncorrelated) signals and truly complex ones.^52,190,191^ Extensive information on these measures, including details of algorithms, tutorials, and examples of their application is provided at Research Resource for Complex Physiologic Signals ([www.physionet.org](http://www.physionet.org)). This website is sponsored by NIH, and was developed by members of our team. |

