### Statistical Considerations

| ***Sample Size Justification:*** Our analysis will be based on a longitudinal regression analysis in which we do not have an estimate of the within-participant correlations. In the worst case, the two follow-up measures provide no more information than a single follow-up, and the power calculation is equivalent to that for a simple t-test. With 30 participants in each group, we would have 50% power to detect an effect size of 0.52 (i.e., the sample size provides 50% sensitivity to detect a difference between groups .52 times the standard deviation of the outcome measure) and 80% power to detect an effect size of 0.74 for each of the main effects. Our primary hypothesis, however, is an interaction effect. Our sample size provides at least 50% power to detect an interaction effect size of 1.03, under this worst-case scenario. At the other extreme, if the two follow-up observations are independent, we will have 50% power to detect an interaction effect size of 0.72 and 80% power to detect an effect size of 1.03. The use of regression models further increases power by accounting for additional sources of variability. In our heart failure study, the mean difference in MSE change between Tai Chi and control was 2.26, which translates to an effect size of 1.2. Preliminary COP data from our Tai Chi for osteopenia study showed a similar effect. Therefore, we think changes of this magnitude will likely be present in the proposed study and our study has adequate power.  For Study Aim 3, we will in essence be comparing the 30 tai chi experts to the 60 novices. After adjusting for the effect of age, we will have 80% power to detect a difference between naïve and tai chi experts of approximately 0.65 times the residual error.  For Study Aim 4, we will be comparing the baseline COP and balance measures in the various age categories (15 participants age 25-35, and 20 participants in each of the older groups). This sample will provide at least 82% power to detect a difference between the young group and the average of the older groups equal to the within-group standard deviation.  ***b. Data Analysis***  *Aim 1*: We are interested in comparing the change over time in the Tai Chi students versus the controls. The primary analysis will use an intention-to-treat paradigm, i.e., participants will be evaluated on the basis of group assigned by randomization without regard to subsequent adherence. Since this is a pilot study, we will not impute values for missing data; however, the statistical models we are using will include all available data. We recognize that some participants may drop out before the follow-up evaluation and that some outcome measures may not be evaluable for some participants. We will make no adjustment for multiple testing. A secondary ‘per-protocol’ analysis will be limited to participants who were compliant (attended 70% of classes and completed at least 70% of home sessions).  Our primary analysis will employ linear mixed effects regression models that examine change over time (i.e., slope) for each outcome measure (i.e., the complexity measures, MSE and detrended fluctuation analysis) for each of the systems (i.e., heart rate, balance and gait). The models will incorporate a random intercept and a random slope for each participant. The models will be of the form:  ****  for individual  in treatment group  where the random intercept , the random slope , and the residual error . The focus of the primary analyses is on , which evaluates whether treatment is associated with the slope over time.  We will also conduct sensitivity analyses that incorporate additional covariates into the models, including age, gender, baseline physical and mental health, BMI, expectancy, and exercise behavior. We are particularly interested in examining age with a focus on assessing whether age substantially reduces the variability of the random effects, i.e., whether it explains a substantial proportion of between-person variability in baseline complexity and slope.  Analyses of secondary outcomes will follow the same general analytic approach. We will use mixed effects models to examine the effects of Tai Chi training over time on physical and cognitive function (exercise capacity, balance, upper and lower extremity strength, cognitive function, and quality of life) and adaptive capacity (change in heart rate, change in COP displacement, change in stride variability).  *Aim 2*: We hypothesize that function and adaptive capacity are associated with complexity. We will first examine the association between complexity measures and function/adaptive capacity at baseline. We will calculate Pearson correlation coefficients between the complexity measures (MSE and detrended fluctuation analysis) and the measures of function/adaptive capacity. To examine the independent association between complexity and function/adaptive capacity, we will fit ordinary least squares regression models using the function/adaptive capacity measures as the dependent variable. Independent variables will include age and sex as well as any other baseline characteristics associated with the function variable. We will add the complexity measure to this model and evaluate the Wald test and the change in R^2^.  We will also investigate whether changes in complexity are associated with changes in function/adaptive capacity. We will fit linear regression models with change in function/adaptive capacity as the dependent variable and change in complexity as the independent variable of interest. Since we will have 2 observations per participant (change at 3 months and change at 6 months), we will use generalized estimating equations methods (GEE) to account for the within-person correlation. Independent variables will include the measure of function/adaptive capacity at baseline, age, sex, treatment group and time (3 vs. 6 month).  Further, we hypothesize that complexity is the primary mediator of the association between Tai Chi and improvements in adaptive capacity. We will examine this using the approach recommended by Judd and Kenny.^193^ For example, to examine whether multi-scale entropy of balance mediates the effect of Tai Chi on center of pressure response to a dual cognitive task among the older participants, we will fit 3 regression models: regress MSE on Tai Chi use; regress COP response on Tai Chi; and regress COP response on MSE and Tai Chi use. The associations seen in these models determine the existence and strength of mediation.  Despite the implicit directionality of our hypotheses, all tests will be two-sided. We recognize that we are examining a moderate number of outcomes in this study. Since it is a pilot study and has limited power, we do not intend to adjust for multiple testing.  *Aim 3:* Our goal is to compare the complexity measures, function, and resilience to perturbations between tai chi experts and those with no tai chi training or only limited training. We expect responsiveness to decrease as a function of age among the tai chi naïve participants (i.e., both randomized groups combined). We hypothesize that tai chi experts will have a generally higher level of responsiveness, and that their responsiveness will decline with age at a slower rate than naïve or novice practitioners. To examine these questions, we will fit linear regression models to the baseline responsiveness measures for all participants:    where TC is an indicator variable for the tai chi experts.  is an estimate of the difference in responsiveness between tai chi experts at age 50,  is an estimate of the change in responsiveness per year for the novice group, and is the difference in rate of change between novices and tai chi experts.  We will fit a similar model to compare the tai chi experts to the naïve and novice groups using the 6-month data for the randomized patients and the baseline data for the tai chi experts. The group variable will be a categorical variable with 3 levels.  *Aim 4:* We will calculate sample means for each of the outcomes in each age group. We will use standard one-way analysis of variance to compare the four groups. If the overall test is significant, we will use Dunnett’s test to compare the young group to each of the older age groups. |

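### One-legged stance is capped at 30 s but modelled linearly: if many participants reach the cap, a real Tai Chi difference is understated and can falsely appear to grow with age

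*Protocol*

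**What the plan says.** **Score.** In section B3 (One-legged standing balance), timing of a trial ends when the position is lost "or when the 30 sec time limit is reached". The analysed value is the best trial: "Three trials will be completed for eyes-open and eyes-closed conditions, and the greatest duration (sec) for each condition will be used for analysis". Table 1 lists the test as "Single leg balance with eyes open and closed", under function and quality of life.

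**Aim 1 model.** Statistical Considerations states: "Our primary analysis will employ linear mixed effects regression models that examine change over time (i.e., slope) for each outcome measure". For the other outcomes: "Analyses of secondary outcomes will follow the same general analytic approach". The function outcomes named there include balance.

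**Aim 3 model.** The stated goal covers complexity, function and resilience. The model sentence reads: "we will fit linear regression models to the baseline responsiveness measures for all participants". Its terms are expert status, age and their interaction.

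**Hypotheses.** H.1.d and H.3.d (section B1) say that the size of the Tai Chi effect, on function among other things, "will be positively correlated with age".

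The protocol does not mention a ceiling, censoring or the share of participants at 30 s, and it gives no stance-time mean, standard deviation or distribution.

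**The concern.** A recorded 30 s means at least 30 s. A linear model reads it as exactly 30 s. Someone who could stand 30 s before training and 45 s after it scores no change, and an expert capable of 60 s ties with a naïve participant who just reaches 30 s.

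The cap bites hardest where times are longest: at younger ages, in the better group and with eyes open. A Tai Chi difference is therefore squeezed near age 50 and left largely intact near age 79. A benefit that is constant in seconds can then look like one that rises with age, which is the pattern that H.1.d and H.3.d predict.

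Two things are at stake for this outcome. One is the effect-size estimate that the pilot is meant to hand on to a larger trial. The other is whether an age interaction can be read as support for those hypotheses. The study population is healthy, starts at age 50 and includes experts with over 5 years of practice, so a substantial share at 30 s with eyes open is plausible. The documents do not establish it.

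**Working it through.** **1. The plan's own power figure.** No figure concerns stance time. The nearest is the t-test power with 30 per group. The noncentral t at two-sided 0.05 (alpha is not stated, so this is assumed) gives 80.5% at effect size 0.74 and 50.8% at 0.52. The stated 80% and 50% reproduce. They refer to an outcome without a ceiling.

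**2. Best of three and the cap.** If one trial reaches 30 s with probability p and trials are independent, P(best = 30 s) = 1 − (1 − p)³. For p = 0.5 this is 1 − 0.125 = 0.875. Correlation between a person's trials lowers it, so 0.875 is an upper figure.

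**3. Mechanism without noise.** Assume a naïve mean of 32 s at age 50, a fall of 0.9 s per year and a constant expert advantage of 8 s.
- Age 50: true 32 against 40 s; recorded 30 against 30 s; gap 0.
- Age 79: fall of 29 × 0.9 = 26.1 s; true 5.9 against 13.9 s; recorded the same; gap 8 s.

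**4. Aim 3 simulation.** From the protocol: 60 naïve, 30 experts, ages 50 to 79, three trials, best kept, cap 30 s. Assumed: person SD 12 s, trial SD 6 s, fall 0.9 s per year, true difference 8 s at every age, times floored at 1 s. The mean at age 50 is varied to move the share at the cap. Nominal one-direction error is 2.5%.

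| Naïve at cap | False interaction, predicted direction: capped | Uncapped | Recovered difference: capped | Uncapped |
|---|---|---|---|---|
| 6% | 1% | 1% | 5.1 s | 5.9 s |
| 11% | 2% | 1% | 5.2 s | 6.6 s |
| 19% | 3–5% | 1% | 5.0 s | 7.2 s |
| 33% | 10% | 2% | 4.2 s | 7.7 s |
| 54% | 17–19% | 2% | 2.8 s | 7.9 s |
| 73% | 16–18% | 2–3% | 1.5 s | 8.0 s |

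Ranges show the spread between repeat runs. In the top rows much of the shortfall from 8 s comes from the 1 s floor, which also pulls the interaction the other way. The effect of the cap is the gap between the capped and uncapped columns. A Tobit model brings the false-interaction rate to about 3–4%. With a true difference of 0, the capped rate is 2–4%.

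**5. Aim 1, different assumptions.** Person SD 8 s, trial SD 5 s, true gain 5 s at every age, 30 per arm. Age-50 mean and yearly fall: low 18 s and 0.4 s; moderate 28 s and 0.6 s; high 36 s and 0.7 s.

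| Scenario | At cap at baseline, ages 50–59 / 60–69 / 70–79 | Observed gain (s) | Age-by-treatment rejections (two-sided) |
|---|---|---|---|
| Low | 14 / 6 / 2% | 3.9 / 4.4 / 4.5 | 6% |
| Moderate | 46 / 23 / 8% | 2.1 / 3.4 / 4.3 | 13% |
| High | 77 / 49 / 21% | 0.8 / 2.0 / 3.5 | 25% |

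Without the cap, rejections run at about 4–6%. In the moderate and high scenarios nearly all rejections have the predicted sign. For a true 4 s gain, power for the group effect is 81–82% uncapped and 78%, 66% and 48% capped.

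**The case against.** **The cap alone does not create an age effect.** A reader might infer that a positive Tai Chi-by-age result can arise from the 30 s limit by itself. It cannot: with no Tai Chi difference, the predicted-direction rate stays at 2–4%. The cap changes how a real difference appears to vary with age.

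**The share at 30 s is unknown.** The low scenario shows almost no harm. Eyes-open and eyes-closed scores are analysed separately, and the harder eyes-closed test probably has fewer participants at the cap. This stands, and the size can only be given as a range.

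**The result assumes a benefit constant in seconds.** With a proportional benefit (times multiplied by 1.4, lognormal), predicted-direction rejections on the capped score were 1.5% with 15% at the cap and 7.9% with 40%. Uncapped scores then gave 12–15% significant interactions in the opposite direction. The Tobit figure of 3–4% comes from data that fit its own assumptions. Both limits stand.

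**The tests are only partly written out.** Aim 1 specifies no age-by-treatment term; age enters as a sensitivity covariate. The Aim 3 model sentence refers to responsiveness, and its use for stance time is inferred from the aim's goal, which names function. This narrows the point but does not remove it, because H.1.d and H.3.d both name function.

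**Best of three is a legitimate score.** It matches Table 1, and the mean of three still leaves false interactions in about 6–19% of trials. A reader might blame the scoring rule, but the age artefact comes from treating 30 s as an exact time. Replacing the score is not required.

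**A separate analysis plan may deal with the ceiling.** It might, and it is not at hand. The protocol nevertheless fixes both the score and the linear approach.

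**Conclusion.** The point holds in conditional form. If roughly a third or more of participants reach 30 s, a real Tai Chi difference on this test is clearly understated. If that difference is about equal in seconds across ages, the linear model can also show it growing with age when it does not. Under the Aim 3 assumptions, the false predicted-direction rate is about 10% with 33% of naïve participants at the cap and about 18% with 54 to 73%, against 2.5% nominal. The recovered difference drops to about 1.5 s of 8 s at the top of that range. At about 20% or fewer the false age pattern is negligible to small (1–5%), although some attenuation of the difference remains.

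All stance-time inputs are assumed. The documents do not support saying that the ceiling will be common, that it affects eyes-closed times equally, or that it produces an age effect where Tai Chi has none. This is a minor-to-moderate point on one secondary outcome of a pilot. The primary complexity outcomes are unaffected.

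**What to change.** For one-legged stance, eyes open and eyes closed separately:

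1. Keep the best of three as the stated score. The mean of the three trials may be added as a supportive score; the protocol already averages repeats for grip strength and Timed Up and Go.
2. Report the share at 30 s by arm, visit and age stratum.
3. For any age interaction on this outcome, and as a sensitivity analysis of the group effects, fit a model that treats 30 s as right-censored (Tobit, with a participant random effect for repeated visits).
4. State that an age interaction from the linear model alone will not be taken as support for H.1.d or H.3.d on this outcome.

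The cost is analysis wording and a little programming, with no new testing. The downside is that the censored model assumes a distribution above 30 s and becomes imprecise when most scores are at the cap. The table in item 2 shows the reader when that is so.
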